## 7. Risk Management and Contingency Planning

To ensure patient safety and address potential risks associated with home-based cardiac telerehabilitation, a structured risk management strategy has been integrated into the TELEREHAB-HF protocol.

Each telerehabilitation session is supervised in real-time by a trained physiotherapist through a digital platform that continuously monitors vital signs using wearable medical-grade sensors. The system tracks SpO_2_, HR, and BP, and provides automatic alerts when pre-defined clinical thresholds are exceeded.

Safety thresholds triggering immediate session interruption and medical evaluation include [1,2,28]:Borg Dyspnea Scale ≥ 8/10Rate of Perceived Exertion ≥ 18/20Resting HR > 120 bpm or <50 bpmSystolic BP > 180 mmHg or <70 mmHgDiastolic BP > 100 mmHg or <50 mmHgSpO_2_ < 88%Sudden fall, acute chest pain, neurological symptoms (e.g., diplopia, motor/sensory deficits, aphasia), altered consciousness

In such events, the physiotherapist halts the session immediately and activates the emergency response protocol, which may include referral to the cardiologist or activation of local emergency medical services (EMS/118).

In case of technical malfunctions or persistent connectivity issues, a fallback mechanism is in place: patients are offered a transition to standard in-person rehabilitation sessions to ensure therapeutic continuity.

All patients receive initial in-person training to become familiar with the devices and the protocol. Those with limited digital literacy are required to have caregiver support as a condition for inclusion. Continuous technical assistance is available throughout the intervention period.

Clinical and biometric data are stored in a secure, encrypted repository, compliant with data protection regulations, ensuring traceability and safety monitoring.

This integrated safety protocol and contingency plan aim to minimize clinical and operational risks, optimize adherence, and ensure high standards of care throughout the rehabilitation pathway (Figure 5).

## 8. Outcomes

Both groups will undergo standardized assessments at baseline (T0), mid-treatment (4 weeks, T1), post-treatment (8 weeks, T2), and at follow-up timepoints (16 weeks, T3; 24 weeks, T4). Evaluations will include cardiopulmonary functional performance, echocardiographic measurements, biochemical markers, cognitive function, and QoL (Table 3).

The primary outcome of the study is the improvement in functional capacity, assessed as a ≥10% increase in VO_2_max, measured via CPET at 8 weeks (T2).

Secondary outcomes include:QoL: Assessed using the KCCQ-12 and SF-36 at each timepoint.Biochemical parameters: Changes in BNP, NT-proBNP, creatinine, eGFR, serum electrolytes (sodium, potassium, chloride), glucose, and lipid profile.Functional assessments: Performance on the 6MWT and SPPB.Cognitive status: Assessed with the MMSE.Echocardiographic parameters: Left ventricular ejection fraction (LVEF), diastolic function indices (E/A—Ratio of early E to late A ventricular filling velocities; E/e’—Ratio of early transmitral flow velocity to early diastolic mitral annular velocity), and right ventricular function (TAPSE—Tricuspid Annular Plane Systolic Excursion, RVs’—Right Ventricular Systolic Velocity).Adverse events: Monitoring of any complications related to training or telemonitoring (e.g., hypotension, arrhythmias, device issues).

These outcome measures will allow for a comprehensive and longitudinal evaluation of the effects of both in-person and telehealth cardiac rehabilitation on patients with chronic heart failure.

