## Abstract

**Background:** Despite strong guideline recommendations, participation in cardiac rehabilitation (CR) among patients with chronic heart failure (CHF) remains low due to logistical, geographical, and psychosocial barriers. Telerehabilitation may help overcome these limitations by offering remote, structured exercise programs supported by digital technologies. **Objective:** The TELEREHAB-HF study aims to evaluate the efficacy of an 8-week, home-based cardiac telerehabilitation program compared to standard in-person rehabilitation in patients with CHF. **Methods:** This is a prospective, controlled cohort study involving 220 adult patients with CHF (NYHA class I–III) clinically stable and on optimized therapy. Participants are assigned to either a telerehabilitation group (remote CR via a digital platform with wearable sensors and real-time physiotherapist supervision) or a standard in-person rehabilitation group. The primary outcome is the change in peak oxygen uptake (VO_2_max) at 8 weeks. Secondary outcomes include quality of life, functional performance, biochemical and echocardiographic parameters, and cognitive function, assessed at baseline and at 4, 8, 16, and 24 weeks. **Expected Results**: We hypothesize that telerehabilitation will be non-inferior to standard CR in improving functional capacity and secondary outcomes, with additional benefits in accessibility and adherence. Data from remote monitoring may also support a translational “rehabilomics” approach to exploring exercise-induced biomarker changes. **Conclusions:** This study seeks to assess the clinical effectiveness, safety, and feasibility of a home-based telerehabilitation model for CHF, with the goal of informing future strategies for broader implementation and personalized rehabilitation. Trial Registration: ClinicalTrials.gov Identifier: NCT07023536

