## 2. Methods

### Study Design and Population

The TELEREHAB-HF study is a single-center, prospective, observational, non-pharmacological cohort trial designed to evaluate the clinical efficacy of a home-based, supervised cardiac telerehabilitation program in patients with CHF. The trial will be conducted at the tertiary care center Azienda Ospedaliera Universitaria (AOU) “San Giovanni di Dio e Ruggi d’Aragona” in Salerno, Italy, in collaboration with the University of Salerno. The study aims to enroll 220 adult patients (≥18 years) with a confirmed diagnosis of CHF—classified as heart failure with reduced ejection fraction (HFrEF), heart failure with mildly reduced ejection fraction (HFmrEF), or heart failure with preserved ejection fraction (HFpEF)—and functional class I to III according to the New York Heart Association (NYHA) classification. All participants must be clinically stable and on optimized medical therapy for at least one month prior to enrollment (Figure 1).

Participants will be allocated to the telerehabilitation or standard rehabilitation arm based on patient preference and logistical eligibility (e.g., home safety, access to digital devices, internet connectivity). Although this approach does not involve randomization, both groups will be enrolled under identical inclusion and exclusion criteria. To mitigate potential selection bias, comprehensive baseline characterization and statistical adjustment (e.g., propensity score methods) will be applied. Patients in the intervention group (TELEREHABILITATION-YES) will undergo an 8-week individualized cardiac rehabilitation program performed at home, supported by the Khymeia Virtual Reality Rehabilitation System (VRRS). The program includes real-time video-supervised sessions with a physiotherapist, and continuous monitoring through medical-grade wearable sensors that collect electrocardiogram (ECG), heart rate (HR), peripheral oxygen saturation (SpO_2_), and blood pressure (BP) data. The system also records exercise performance using inertial movement sensors, and all data are transmitted securely to a central digital platform for remote clinical oversight and feedback.

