## 9. Statistical Analysis

### 9.1. Primary Endpoint Analysis

To evaluate the primary endpoint of the study—defined as a ≥10% improvement in VO_2_max at 8 weeks—paired comparisons between baseline and post-intervention values will be performed using a paired t-test for normally distributed data [36,37,38]. For non-normally distributed data, the Wilcoxon Signed-Rank test will be applied. Additionally, the proportion of patients achieving the predefined VO_2_max improvement threshold will be analyzed using logistic regression, with “Rehabilitation Type (Telerehabilitation vs. Standard)” as the main predictor. The model will be adjusted for clinically relevant covariates identified through baseline comparisons using ANOVA or chi-square tests. Odds ratios and 90% confidence intervals will be reported.

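### Baseline VO2max is the denominator of the primary endpoint, but the between-arm model includes it only if a baseline significance test picks it out

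*Protocol article*

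**What the plan says.** Section 8 of the protocol article defines the primary outcome as functional capacity "assessed as a ≥10% increase in VO_2_max", measured by cardiopulmonary exercise testing at 8 weeks. The abstract words it as a continuous quantity: "The primary outcome is the change in peak oxygen uptake (VO_2_max) at 8 weeks".

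On allocation, Section 2 (Study Design and Population) states: "Participants will be allocated to the telerehabilitation or standard rehabilitation arm based on patient preference and logistical eligibility". The population covers all ejection-fraction classes of heart failure and NYHA I to III. Section 2 also promises statistical adjustment for selection bias, with propensity scores as an example, but names no variables.

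Section 9.1 sets out the between-arm analysis of the primary endpoint: "the proportion of patients achieving the predefined VO_2_max improvement threshold will be analyzed using logistic regression". Study arm is the explanatory variable of interest in that model. The section then fixes how covariates are chosen: "The model will be adjusted for clinically relevant covariates identified through baseline comparisons using ANOVA or chi-square tests". The paired t-test or Wilcoxon test in the same section compares baseline with post-treatment values, not one arm with the other. Baseline VO2max is measured at T0 (Table 3), but no section requires it in the logistic model.

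**The concern.** A relative threshold asks for a different absolute gain at each baseline: 1.0 mL/kg/min for a patient starting at 10, and 2.4 for one starting at 24. In a population this broad, with self-selected arms, mean baseline VO2max may differ between arms. If training then adds the same number of mL/kg/min in both, the arm with the lower baseline shows more responders, and the odds ratio partly reflects who chose which arm.

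The covariate most closely tied to the endpoint is thus admitted or left out according to a p-value. The abstract hypothesises non-inferiority, and for a claim of that kind a shift of a few percentage points can matter.

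**Working it through.** **Inputs from the article.** The threshold is 10% of the patient's own baseline. The sample is 200 before dropout (Section 9.3). The allocation ratio is not stated; 100 per arm is assumed.

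**The plan's own figure.** The 200 cannot be reproduced, because Section 9.3 gives no SD, baseline mean or responder rate. At two-sided 5% and 90% power, 100 per arm corresponds to a standardised difference of (1.960 + 1.282) × √(2/100) = 0.458. The 200 is used below only for the arm size.

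**Assumed, because the article gives no VO2max figures.** Baseline SD 4 mL/kg/min; mean gain 1.0 to 2.0; gain SD 1.0 to 2.0; test-error SD 0 or 1; baseline tests at 5%.

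**Step 1: one patient.** Take true baseline T, true gain 1.5 and error SD 1 on each test. Response means that follow-up is at least 1.1 × measured baseline. The margin has mean 1.5 − 0.1T and SD √(1 + 1.21) = 1.487, so P = Φ((1.5 − 0.1T)/1.487). This gives 58% at T = 12, 50% at 15 and 42% at 18.

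**Step 2: one arm, equal absolute gain, no test error.** Responder rate = Φ((g − 0.1μ)/√(s² + 0.01 × 4²)), with mean baseline μ, mean gain g and gain SD s. For g = 1.5 and μ = 16 versus 17:

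| s | μ = 16 | μ = 17 | gap (points) |
|---|---|---|---|
| 1.0 | 46.3% | 42.6% | 3.7 |
| 1.5 | 47.4% | 44.9% | 2.6 |
| 2.0 | 48.0% | 46.1% | 2.0 |

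With g of 1.0 or 2.0 the gap stays between about 2 and 4 points.

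**Step 3: will the baseline test flag the imbalance?** The standard error of the baseline difference is 4 × √(2/100) = 0.566. The chance of p < 0.05 is about Φ(d/0.566 − 1.96):

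- d = 0.5: 14%
- d = 1: 42%
- d = 1.5: 76%
- d = 2: 94%

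The smallest observed difference that is flagged is 1.96 × 0.566 = 1.1 mL/kg/min, so an unflagged observed difference is at most about that size.

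**Step 4: what the stated rule achieves.** Simulation of 1,500 trials, 100 per arm, equal gain 1.6, gain SD 1.5. The entries are null odds ratios for the arm with the higher baseline; 1.00 is correct.

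| imbalance | error SD | no baseline term | test-then-adjust | always adjusted |
|---|---|---|---|---|
| 1 | 0 | 0.91 | 0.98 | 1.02 |
| 2 | 0 | 0.80 | 0.98 | 0.98 |
| 1 | 1 | 0.93 | 1.01 | 1.06 |
| 2 | 1 | 0.87 | 1.10 | 1.11 |

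Under test-then-adjust, false rejection at nominal 5% in these four rows is 4.4%, 5.5%, 5.4% and 5.4%. These averages mix flagged and unflagged trials. With a 1 mL/kg/min imbalance, gain SD 1 and no test error, the unflagged trials alone had a mean null odds ratio of 0.91.

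**Step 5: equal percentage gain.** If the percentage gain has the same distribution at every baseline (say mean 10%, SD 10%), the responder rate is 50% at every baseline and the artefact is zero.

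**The case against.** Four points can be made against the concern.

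- **The planned model is adjusted.** A reader might infer that the arms are compared with no allowance for baseline, and quote a shift of 4 to 8 points for a 2 mL/kg/min imbalance. The article does not support that: Section 9.1 adjusts for flagged covariates, and an imbalance of that size would be flagged about 94% of the time. This stands and limits the concern to imbalances of about 1 mL/kg/min or less. The covariate must also be judged clinically relevant, but baseline VO2max is an obvious candidate.
- **Equal absolute gain is an assumption.** Training intensity is set relative to each patient's capacity (Section 3), and the protocol itself defines benefit as a percentage. On that scale the artefact disappears. This stands as a condition. Nothing in the article settles which pattern holds.
- **Forced adjustment is not harmless.** A baseline that reads low by chance makes response easier, so measured baseline predicts response even when true baseline does not. With error SD 1 and a 2 mL/kg/min imbalance, the adjusted null odds ratio is about 1.10 to 1.13 under either gain pattern, and up to 1.15 in some settings. Under proportional gains the unadjusted ratio would have been 1.00. This stands and must be disclosed with the fix.
- **Naming a covariate belongs in an analysis plan.** This does not stand. Section 9.1 does not leave the choice open: it sets a rule under which the endpoint's own denominator can stay out. The propensity-score remark in Section 2 could cover baseline VO2max but does not commit to it.

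**Conclusion.** The concern holds as a modest weakness in the covariate rule. The endpoint depends on baseline VO2max by construction, the arms are self-selected, and inclusion of that variable in the only between-arm model depends on a test that misses a 1 mL/kg/min imbalance more often than not (flagged about 42% of the time). If gains are equal in mL/kg/min, such a miss moves responder rates by about 2 to 4 points, against the arm with the higher baseline. The article does not show which arm that would be.

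Averaged over trials, the stated rule removes most of the bias: without test error, the null odds ratio is about 0.98 to 1.01 and false rejection is 4% to 6%. The size rests on an assumed baseline SD of 4, 100 per arm, 5% baseline tests and the assumed gain and error values. A reader should not take it that the artefact arises whatever the pattern of gains, or that adjustment removes it completely.

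**What to change.** In Section 9.1:

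1. Prespecify baseline VO2max as a continuous term in the responder model, and in any propensity score, regardless of baseline test results.
2. Report the responder rate of each arm standardised to the pooled baseline VO2max distribution.
3. Add a between-arm comparison of continuous 8-week VO2max adjusted for baseline. This fits the abstract's wording of the outcome as a change.
4. Show the adjusted and unadjusted responder results side by side as a sensitivity check. State that test error in the measured baseline can leave a small bias in the opposite direction (null odds ratio about 1.03 to 1.13 for imbalances of 1 to 2 mL/kg/min at error SD 1).

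The continuous comparison shares this limit to a small degree. With true SD 4 and error SD 1, the reliability of the baseline is 16/17 = 0.94. Under equal absolute gains that leaves 1 − 0.94 = about 0.06 mL/kg/min per 1 mL/kg/min of imbalance.

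The cost is a few sentences and one degree of freedom in the model. Baseline VO2max is already measured at T0, so no data collection changes. The price in interpretation is the residual bias in item 4, which is why both results should be shown.

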## 3. Groups and Interventions

Participants enrolled in the study will be allocated to one of two groups based on their voluntary acceptance of the telerehabilitation modality:1.TELEREHABILITATION—YES (Remote Group)2.TELEREHABILITATION—NO (In-Person Group)

Both groups will undergo an 8-week individualized CR program based on international guidelines for heart failure rehabilitation [29]. The intervention includes a combined training protocol delivered 5 times per week for the first 4 weeks, and 3 times per week for the subsequent 4 weeks. Each session lasts approximately 60 min and is structured as follows (Table 2):10 min of interval training (warm-up) including flexibility, breathing, and coordination exercises;40 min of endurance training using a stationary bicycle, aiming at 70% of VO_2_ peak (as determined by baseline CPET) or 75–80% of maximum HR if CPET is not available [30,31,32,33,34];10 min of cool-down exercises with stretching and breathing techniques.

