## 4. In-Person Group (TELEREHABILITATION—NO)

Sessions are conducted under the direct supervision of a physiotherapist at the cardiac rehabilitation unit of the A.O.U. San Giovanni di Dio e Ruggi d’Aragona. Vital parameters (BP, HR, SpO_2_) are manually recorded; perception of fatigue and dyspnea is assessed using the Borg and Rate of Perceived Exertion (RPE) scales [23,35]. No technological devices are used for remote monitoring.

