## 5. Remote Group (TELEREHABILITATION—YES)

Sessions are delivered synchronously at the patient’s home via a digital telerehabilitation platform (Khymeia VRRS Home System), enabling real-time audiovisual interaction with the physiotherapist. Patients are equipped with a home-based kit including a tablet, wearable sensors (K-RING, K-SENSOR), a spirometer (K-SPIRO), and a health monitor capable of recording ECG, HR, SpO_2_, and BP. The sensors adopted in the TELEREHAB-HF protocol were selected to ensure clinically relevant, real-time, and multidimensional monitoring of patients during home-based cardiac rehabilitation. These sensors were preferred over alternative solutions (e.g., consumer-grade smartwatches, standalone wearable ECG monitors, or optical motion capture systems) due to their medical-grade certification, full integration with the Khymeia VRRS platform, and ability to support both synchronous feedback and asynchronous data collection. Their interoperability, reliability, and user-friendliness in non-clinical environments make them particularly suitable for patients with chronic cardiovascular conditions undergoing home-based telerehabilitation.

All data are transmitted and stored securely in compliance with data protection regulations. Movement execution is monitored through inertial sensors, and real-time feedback is provided to ensure exercise accuracy. Borg and RPE scales are administered online during sessions.

In both groups, outcome measures (Anthropometric measures, CPET, 6MWT, SPPB, echocardiography, QoL questionnaires, laboratory tests, and MMSE) will be collected at baseline (T = 0), during the intervention (T = 1, at 4 weeks), post-intervention (T = 2, at 8 weeks), and during follow-up at 16 (T = 3) and 24 weeks (T = 4). Patients in the telerehabilitation group experiencing clinical or technical issues may transition to in-person sessions to ensure therapeutic continuity.

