## 6. Technological Solution Used for the TELEREHABILITATION—YES Group

The technology used to deliver the telerehabilitation program is the Khymeia System (Virtual Reality Rehabilitation System, VRRS by Khymeia Group, Noventa Padovana, Italy; https://khymeia.com/it/ accessed on 24 February 2025). It is a Class I medical device designed for remote rehabilitation.

During the initial in-person training phase with the VRRS EVO system, the following components and accessories are used.

VRRS EVO system (Figure 2), which includes:A processing unit enclosed in a dedicated cabinet, a capacitive touchscreen LCD monitor, and a low-intensity electromagnetic field generatorWireless 3D passive sensors worn by the patient, detecting position and orientation (6 degrees of freedom) through the electromagnetic fieldThe number of sensors is adapted to specific rehabilitation needs

K-SENSOR: inertial sensors for monitoring movement parametersK-Sensor bands: to support accurate and easy placement of sensors on the limbs during exercisesK-RING: a wearable sensor for continuous monitoring of HR and SpO_2_K-SPIRO: a spirometer for guided respiratory exercises

Health Monitor: for measuring, displaying, and recording body temperature, BP, and single-lead ECG in home or clinical settings.

During the home-based physiotherapy program, following the in-person familiarization with VRRS EVO, the following components are also used:

TeleCockpit System (Figure 3): a high-tech control station for managing all telerehabilitation-related processes, protocols, and sessions. It includes: a height-adjustable, motorized workstation; a control terminal with keyboard and mouse for managing video conferencing and remote control sessions; dual-monitor setup; professional-grade audio-video conferencing system with camera and microphone; professional remote control system.

VRRS Home Kit (Figure 4), enabling home telerehabilitation. This includes:Tablet deviceK-SENSOR inertial sensorsK-Sensor bands for proper placement on limbsK-RING for continuous HR and SpO_2_K-SPIRO spirometer for breathing exercisesHealth Monitor for measuring and storing body temperature, BP, and ECG (single lead)

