### 9.2. Secondary Endpoint Analysis

Continuous variables will be presented as mean ± standard deviation for normally distributed variables, and as median and interquartile range for those with non-normal distribution. Categorical data will be expressed as absolute numbers and percentages. The Shapiro–Wilk test will be used to assess normality.

For repeated measurements (e.g., QoL scores, biochemical markers, functional parameters), comparisons across timepoints (T0, T1, T2, T3, T4) will be conducted using one-way repeated measures ANOVA for normally distributed data, or Friedman test for non-parametric data.For post hoc comparisons, Bonferroni correction will be applied to control for type I error.Categorical variables (e.g., proportion of patients with adverse events) will be compared using the Pearson chi-square test or Fisher’s exact test where appropriate.

A two-sided *p*-value < 0.05 will be considered statistically significant for all final analyses.

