Secondary	Change in Serum Potassium	mmol/L	Biochemical	Important for assessing treatment safety (e.g., diuretics, ACE inhibitors) and arrhythmic risk	✔		✔	✔	✔
Secondary	Change in Serum Chloride	mmol/L	Biochemical	Important for assessing treatment safety (e.g., diuretics, ACE inhibitors) and arrhythmic risk	✔		✔	✔	✔
Secondary	Change in Glucose	mg/dL	Biochemical	Cardiovascular risk profile monitoring and potential metabolic benefits from exercise	✔		✔	✔	✔
Secondary	Change in Lipids	mg/dL	Biochemical	Cardiovascular risk profile monitoring and potential metabolic benefits from exercise	✔		✔	✔	✔
Secondary	Change in LVEF	%	Echocardiographic	Quantifies systolic and diastolic function; allows tracking of cardiac remodeling and hemodynamic response to rehabilitation	✔		✔	✔	✔
Secondary	Change in E/A and E/e’	Ratio	Echocardiographic	Quantifies systolic and diastolic function; allows tracking of cardiac remodeling and hemodynamic response to rehabilitation	✔		✔	✔	✔
Secondary	Change in TAPSE, RVs’	mm/cm/s	Echocardiographic	Quantifies systolic and diastolic function; allows tracking of cardiac remodeling and hemodynamic response to rehabilitation	✔		✔	✔	✔
Secondary	Adverse Events	Number of events over the total number of treatments administered	Safety	Monitors safety and tolerability of both telerehabilitation and standard rehabilitation interventions		✔	✔	✔	✔

Abbreviations: 6MWT—6-Minute Walk Test; ACE- Angiotensin-Converting Enzyme; BNP—B-type Natriuretic Peptide; CPET—Cardiopulmonary Exercise Testing; CHF—Chronic heart failure; E/A—Ratio of early (E) to late (A) ventricular filling velocities; E/e’—Ratio of early transmitral flow velocity to early diastolic mitral annular velocity; ECG—Electrocardiogram; eGFR—Estimated Glomerular Filtration Rate; KCCQ-12—Kansas City Cardiomyopathy Questionnaire—12 items; LVEF—Left Ventricular Ejection Fraction; MMSE—Mini-Mental State Examination; NT-proBNP—N-terminal pro B-type Natriuretic Peptide; QoL—Quality of life; SF-36—Short Form Health Survey—36 items; SPPB—Short Physical Performance Battery; TAPSE—Tricuspid Annular Plane Systolic Excursion; VO_2_max—Maximal Oxygen Uptake; RVs’—Right Ventricular Systolic Velocity; ✔—timepoints at which the outcome measure was assessed.

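### Device issues, which essentially only the remote arm can have, count as adverse events, and the quantity tested (patients) is not the one Table 3 defines (events per treatment)

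*Protocol article*

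**What the plan says.** All references are to the protocol article.

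- **Definition (section 8, Outcomes).** The adverse-event outcome is "Monitoring of any complications related to training or telemonitoring (e.g., hypotension, arrhythmias, device issues". Clinical complications and equipment problems appear in one list, and no division between them is given.
- **Test (section 9.2, Secondary Endpoint Analysis).** "Categorical variables (e.g., proportion of patients with adverse events) will be compared using the Pearson chi-square test", with Fisher's exact test as the alternative. The sentence does not name the groups compared.
- **Measure (Table 3).** The unit for adverse events is "Number of events over the total number of treatments administered", and the stated rationale is "Monitors safety and tolerability of both telerehabilitation and standard rehabilitation interventions".
- **Exposure to devices (sections 4 and 5).** For the in-person arm: "No technological devices are used for remote monitoring". The remote arm receives a home kit of tablet, wearable sensors, spirometer and health monitor.
- **Number of treatments (section 3).** Training is "delivered 5 times per week for the first 4 weeks, and 3 times per week for the subsequent 4 weeks" in both arms.
- **Change of mode (section 5).** "Patients in the telerehabilitation group experiencing clinical or technical issues may transition to in-person sessions".

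**The concern.** There are two linked problems.

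First, the outcome contains a component that one arm can accumulate and the other essentially cannot. If device issues and clinical events are counted together, two arms with the same clinical safety will show different proportions of patients with an event, always with the excess on the remote side.

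Second, the article gives two different quantities for one outcome. Section 9.2 counts each patient once; Table 3 counts every event and divides by sessions delivered. A chi-square or Fisher test on patients does not analyse the Table 3 rate, and the article does not say which one carries the safety conclusion. The two can point in opposite directions, so the conclusion could depend on a choice made once the data are known.

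This matters because safety is among the study's stated aims, and section 11 (Discussion) says a low adverse-event rate may support feasibility.

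**Working it through.** The article gives no adverse-event rate, power or sample size for this outcome, so there is no planned figure to reproduce. The calculation shows how large the effect could be under stated assumptions.

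**Inputs from the article**
- Two-sided significance level 0.05 (section 9.2).
- 200 evaluable patients (section 9.3).
- Sessions per patient: 5 × 4 + 3 × 4 = 32 (section 3).

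**Assumptions**
- 100 patients per arm. Allocation follows preference and logistics, so the real split is not fixed.
- The same proportion *p* of patients with a clinical adverse event in both arms: 5%, 10% or 20%.
- An independent proportion *d* of remote patients with at least one device issue: 0% to 10%.

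**Step 1: effect of pooling.** The remote proportion is *p* + (1 − *p*)*d*; the in-person proportion is *p*. With *p* = *d* = 10%, this is 0.10 + 0.90 × 0.10 = 19% against 10%. The chance of a significant uncorrected chi-square result, by exact enumeration of the two binomial distributions, is:

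| *d* | *p* = 5% | *p* = 10% | *p* = 20% |
|---|---|---|---|
| 0% | 4.4% | 5.2% | 5.1% |
| 1% | 5.4% | 5.7% | 5.3% |
| 2% | 8.1% | 7.1% | 6.0% |
| 5% | 25% | 16% | 11% |
| 10% | 65% | 45% | 26% |

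Fisher's exact test gives lower values. For *p* = 5% and 10% respectively they are 4.7% and 4.3% at *d* = 2%, 17% and 12% at *d* = 5%, and 55% and 37% at *d* = 10%.

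With *p* = *d* = 10% and unequal arms, the chi-square figure is 42% for 60 remote and 140 in person, and 33% for 140 remote and 60 in person.

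**Step 2: what these fault rates mean per session.** If faults are independent across 32 sessions, the per-session rate is 1 − (1 − *d*)^(1/32). For *d* = 2% this is about 1 fault in 1,584 sessions; for 5%, 1 in 624; for 10%, 1 in 304. If faults cluster in a few patients, the same per-session rate touches fewer patients and *d* is smaller.

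**Step 3: the two measures compared.** If all sessions are delivered, 100 patients receive 100 × 32 = 3,200 treatments. Suppose one arm has 10 patients with 1 event each and the other has 5 patients with 4 events each.
- Patients with an event: 10/100 = 10% against 5/100 = 5%.
- Events per treatment: 10/3,200 = 3.1 per 1,000 against 20/3,200 = 6.3 per 1,000.

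The first arm looks worse on the section 9.2 quantity and better on the Table 3 quantity. The example is constructed, but it shows that the measures are not interchangeable.

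**The case against.** **The pooled between-arm test is inferred.** Section 8 gives device issues only as an example, and section 9.2 gives a general rule for categorical variables without naming groups. A full protocol or analysis plan could tabulate event types separately. This stands in part: pooling across arms is the natural reading, because Table 3 says the outcome covers both interventions, but it is not stated outright. It does not answer the mismatch of measures, since the article itself states both.

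**Device failure is part of the telerehabilitation package.** It can end remote delivery, so counting it is defensible. If device issues are meant to count, the arms truly differ, and the rejection rates above are power rather than false positives. That is fair, and it is why device issues should be reported rather than dropped. But a lost signal and an arrhythmia are different safety facts, and one pooled proportion cannot separate them.

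**Patients with events and events per exposure are often reported together.** True, and both can be kept. What is missing is which one is tested.

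**Stronger readings that the article does not support.**
- A reader might infer detection bias, because continuous sensing ("a wearable sensor for continuous monitoring of HR and SpO_2") and automatic alerts are described only for the remote arm. But in-person patients are directly supervised, blood pressure, heart rate and oxygen saturation are recorded in both arms, and nothing excludes ECG on the unit. Neither the existence nor the size of such a bias can be shown.
- A reader might also see a contradiction in Table 3 ticking adverse events at T3 and T4, after training has ended. Later events can still be counted over the treatments already given.

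**Conclusion.** The concern holds in a limited form. The outcome as defined includes equipment faults that essentially one arm alone can have, and the quantity tested in section 9.2 is not the quantity defined in Table 3. Where the test is a pooled comparison between arms, the direction of the tilt, against telerehabilitation, needs no assumed rate.

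Its size does. It is negligible if 1% to 2% of remote patients have a device issue, and material at 5% to 10%. These figures rest on assumed event rates, independence of clinical and device events, and 100 patients per arm; they are smaller with Fisher's test.

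One secondary safety outcome is affected. The primary analysis, significance level and sample size are not. The point is worth correcting because the correction is nearly free.

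**What to change.** 1. Make the tested measure the proportion of patients with at least one clinical adverse event over a stated window, for example T0 to T2. Name the comparison as between arms, and count patients who move to in-person sessions in their original group.
2. Report device and connectivity issues separately and descriptively, per remote session.
3. Keep the Table 3 rate, events per treatment administered, as a descriptive measure, and label it so.

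**Cost.** Changes of wording in section 8, section 9.2 and Table 3, and a record of the mode of each session so that remote sessions can be counted after a change of mode. No extra patients or visits are needed. The downside is that fewer events enter the test, so its interval is wider, and device problems are then judged as feasibility rather than within the safety comparison.
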